### Sample Size

For estimation of sample size, we did not find any study regarding self-care in Iranian population. However, a study has demonstrated that self-care activities and quality of life are correlated [32]. Therefore, sample size for this study was estimated based on the similar study in the country of Iran [33]. A sample size of 60, corresponding to the formula, has been estimated. Considering confidence interval 95%, a power of 80%, and a dropout rate of 20%, 72 subjects will be required. A total of 36 subjects will be randomly assigned to the intervention arm to receive the DPHR tool, and the remaining 36 subjects assigned to the control to receive the usual care.

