### Study Design

A four-phase approach, including a systematic review of evidence regarding DPHR development, usability testing, iterative refinement, and intervention evaluation will be utilized. A randomized controlled trial (RCT) with a 2-arm parallel design and allocation ratio of 1:1 will be used to evaluate the impact of DPHRs on self-care. Repeated assessments will be conducted at two time points, including baseline and postintervention, over a 4-month trial period. The patients in the intervention group will be allowed access to the Web-based app, while those in the control group will be receiving usual care throughout the study period.

The DPHR interface will be designed in three types, covering our three groups of users including the participating patients, the clinic staff, and the physicians. The chief researcher will be the system administrator. Reminders via a short message service (SMS), telephone contact, and email will be used for visiting the website.

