### Analysis Plan

All analyses will be 2-tailed and statistical significance is considered as a *P* value of ≤.05. Data will be analyzed using SPSS. χ^2^ test will be used for determining differences in subject groups based on data collected from baseline, and postintervention (significance interval of 95% will be considered). A *t* test will be used to compare the control and intervention groups, while a chi-square test will be used for continuous and categorical variables, respectively. The distribution of variables, website usage statistics, and website user satisfaction are examined using descriptive analysis.

Examination of the impact of the DPHR tool on self-care will be performed using a linear mixed model at the end of the trial period. The longitudinal nature of data collection will result in a repeat in the measure of analysis of variance using data from all trial assessment points. Missing values will be handled using multiple imputation [35]. All analyses will be done according to intention-to-treat principle.

Before inferential analysis, the homogeneity of variances of distributions in the study groups will be confirmed. The sequential logistic regression will be used for adjusting baseline characteristics and possible confounders. Dropouts from the study will be measured by no-use of the app tool for more than one month. Also, participants in the intervention group must enter blood glucose measurements at home (FBS, bedtime, 2 hours after lunch, and 2 hours after dinner) at least four times a week, otherwise, they are eliminated from the trial. The access data will be assessed using the Web server access log.

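### The 72 patients cover 16.7% dropout, not the stated 20%, and the 80% power is not established for the self-care outcome

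*Protocol article*

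**What the plan says.** The Sample Size section starts from a number without dropout: "A sample size of 60, corresponding to the formula, has been estimated". It then reaches the number to randomise: "Considering confidence interval 95%, a power of 80%, and a dropout rate of 20%, 72 subjects will be required". These are split 36 and 36, in line with the "2-arm parallel design and allocation ratio of 1:1" under Study Design. The Analysis Plan fixes the test level: "All analyses will be 2-tailed and statistical significance is considered as a *P* value of ≤.05".

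On where the 60 comes from, the section first reports that no self-care study in the Iranian population was found. It then notes that "self-care activities and quality of life are correlated" and, on that ground, bases the size on a similar Iranian study. The article does not give that study's endpoint, effect or SD, or the size of the correlation.

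Self-care is what the trial sets out to test: it is in the Objective, among the primary outcomes in the Abstract, and in the Study Hypothesis.

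**The concern.** Two separate things in this paragraph do not hold together.

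The first is arithmetic. A dropout rate is a proportion of those randomised, so the number needed is divided by the proportion retained. Here 20% was added to the number needed instead. The plan therefore states three figures (60 required, 20% dropout, 72 randomised) that cannot all be true.

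The second is the basis of the power statement. Power belongs to a particular outcome, through its expected difference and its SD. A correlation between two outcomes says that patients high on one tend to be high on the other. It does not say that an intervention shifts both by the same number of SDs. If the 60 was derived for another outcome, the 80% belongs to that outcome and has not been shown for the self-care score. A reader of the results would take the trial to have been powered for self-care when the article does not show this.

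**Working it through.** **Inputs.** From Sample Size: 60 before dropout, 20% dropout, 80% power, 72 randomised, 36 per arm. From Study Design: 1:1 allocation, so 60 is 30 per arm. From Analysis Plan: two-sided 5%.

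**Reproducing the plan's figure.** 60 × (1 + 0.20) = 72. This matches exactly.

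**The figure that a 20% loss requires.** 60 / (1 − 0.20) = 75. For equal arms, 30 / 0.80 = 37.5, rounded up to 38 per arm, or 76 in total.

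**What 72 delivers.**
- Evaluable after 20% loss: 72 × 0.80 = 57.6, or 28.8 per arm, against the 60 required.
- Loss that still leaves 60: (72 − 60)/72 = 12/72 = 16.7%.

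**Effect on power.** The article gives no effect size, so the 60 itself cannot be re-derived. I solved for the standardised difference d that gives 80% power with 30 per arm, using an unadjusted two-sample t test, two-sided 5% (noncentral t with 2n − 2 degrees of freedom and noncentrality d√(n/2), n per arm). This gives d = 0.736. The normal approximation gives (1.96 + 0.84) × √(2/30) = 0.723. Holding d at 0.736:

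| Evaluable (total) | Per arm | Power |
|---|---|---|
| 60 | 30 | 80.0% |
| 58 | 29 | 78.6% |
| 57.6 | 28.8 | 78.3% |
| 57 | 28.5 | 77.9% |

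The loss is under 2 points at 20% dropout.

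**What can be said about self-care.** No difference or SD for the self-care score is given, so its power cannot be computed. The detectable difference in SD units can be. With the same t test and 80% power, d is 0.749 with 29 per arm (58 evaluable) and 0.670 with 36 per arm (all 72).

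**How much the choice of outcome could matter (assumption, not a finding).** Suppose the standardised effect on self-care is a fraction of the one behind the 60. The documents do not give this fraction. With 60 evaluable:

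| Fraction | Power |
|---|---|
| 1.0 | 80% |
| 0.9 | 71% |
| 0.8 | 61% |
| 0.7 | 50% |
| 0.5 | 29% |

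A fraction above 1 would give more than 80%. The table shows only that the power claim is sensitive to an input the article does not supply.

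**The case against.** **The arithmetic slip changes almost nothing.** Power falls by less than 2 points and no design feature or analysis depends on it. This stands, and it is why the error is minor. The stated combination is still not the one delivered, and correcting it costs a sentence.

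**The substitution is disclosed, and an article may leave the effect size and SD to the full protocol.** Both are fair, and the missing figures are not the complaint. The complaint is that the reason the article does give, a correlation, cannot support a power claim for self-care.

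**Multiple imputation under intention-to-treat makes dropout irrelevant.** This does not stand. Imputation does not in general restore the lost information, and the plan itself inflates for dropout.

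Three stronger readings are tempting, and the article does not support them:
- *That the source study measured quality of life.* This is the likeliest reading, given how the sentence argues, but the article never says so. What it does show is that the size does not rest on Iranian self-care data.
- *That the trial is underpowered for self-care.* With no effect size or SD for self-care, power is unknown. It could be below or above 80%.
- *That the coefficients of 0.47 and 0.4 under Outcome Measure can be used to adjust the detectable difference, for reliability or for baseline.* The article does not say which statistic the 0.47 is or what the 0.4 correlates. It does not give a correlation between baseline and 4 months. Neither figure can carry such a calculation.

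**Conclusion.** The point holds in two parts of different kinds.

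The dropout allowance is wrong on the plan's own figures: 72 covers 16.7%, and 20% would need 75, or 76 for equal arms. This rests only on reading 60 as the total needed after dropout, which the exact match 60 × 1.20 = 72 confirms. Power of about 78% in place of 80% also assumes an unadjusted two-sample t test at the implied 0.74 SD. The planned linear mixed model could behave somewhat differently. The error is minor.

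The 80% power is not established for self-care, because the only link offered between self-care and the source of the sizing is a correlation of unstated size. This is an unsupported claim, not a demonstrated shortfall. A restatement of the paragraph settles both parts, and neither calls the design itself into question.

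The detectable differences of 0.75 SD and 0.67 SD describe what the trial is likely to detect. They should not be read as what a null result would rule out; the confidence interval from the trial will show that.

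**What to change.** Keep 72 and reword the Sample Size paragraph:

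1. State that 72 allows for 16.7% dropout while keeping 60 evaluable, and that with 20% dropout about 57 to 58 are evaluable and power is about 78% at the effect behind the 60.
2. State that the 80% applies to the outcome and effect of the source study, and name that outcome.
3. Add the detectable standardised difference in the self-care score at 80% power, two-sided 5%, under an unadjusted two-sample t test: about 0.75 SD with 58 evaluable and about 0.67 SD with all 72.

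The cost is one paragraph of text, with figures slightly less favourable than those now printed. No extra patients are needed. If the sponsor prefers to keep both the 20% allowance and the 60 evaluable, the number to randomise becomes 75, or 76 for equal arms: three or four more patients.

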### Outcome Measure

The investigators will employ the Summary of Diabetes Self-care Activities Measure-revised for assessing self-care behaviors [34]. A study has reported the validity and reliability of this instrument, with an internal consistency of 0.47 and a correlation of 0.4 [34]. Also, the patient adherence to a planned visit will be measured.

In this study, researchers will examine any potential correlation, rather than cause and effect, between the app usage and the diabetes follow-up clinical indicators. Such indicators which are based on the routine follow-up procedure of diabetes clinics are: fasting blood sugar (FBS); 2-hour postprandial blood sugar; bedtime blood sugar; blood pressure; weight; height; BMI; lipid profile (total cholesterol, triglyceride, HDL, and LDL); and HbA1c.

### Data Collection

One primary outcome and several secondary outcomes will be assessed with several validated assessment tools. Face and content validity of the questionnaire will be assessed through the expert opinions (including two endocrinologists, one health informatics specialist, and one methodologist) and valid literature. Also, the questionnaire will be completed using structured interviews through the person who is not a member of trial team. The subjects will complete the questionnaire on paper.

Each participant will be requested to complete the questionnaire in-person at the reference clinic at the time of the scheduled diabetes follow-up. Statistics on website visits will be obtained using the access logs by the Web server. After the end of the trial period, the participants’ opinions and experiences on the DPHR tool will be assessed using another questionnaire.

### Analysis Plan

All analyses will be 2-tailed and statistical significance is considered as a *P* value of ≤.05. Data will be analyzed using SPSS. χ^2^ test will be used for determining differences in subject groups based on data collected from baseline, and postintervention (significance interval of 95% will be considered). A *t* test will be used to compare the control and intervention groups, while a chi-square test will be used for continuous and categorical variables, respectively. The distribution of variables, website usage statistics, and website user satisfaction are examined using descriptive analysis.

Examination of the impact of the DPHR tool on self-care will be performed using a linear mixed model at the end of the trial period. The longitudinal nature of data collection will result in a repeat in the measure of analysis of variance using data from all trial assessment points. Missing values will be handled using multiple imputation [35]. All analyses will be done according to intention-to-treat principle.

Before inferential analysis, the homogeneity of variances of distributions in the study groups will be confirmed. The sequential logistic regression will be used for adjusting baseline characteristics and possible confounders. Dropouts from the study will be measured by no-use of the app tool for more than one month. Also, participants in the intervention group must enter blood glucose measurements at home (FBS, bedtime, 2 hours after lunch, and 2 hours after dinner) at least four times a week, otherwise, they are eliminated from the trial. The access data will be assessed using the Web server access log.

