## Methods

### Randomization and Blinding

After the provision of informed consent, participants are randomly allocated to the control or intervention arm stratified by gender (male, female), employment status (employed and nonemployed), and age groups (=<30; 30-50; and =>50 years of age), that is, the covariate adaptive random allocation is considered. The random allocation sequence will be done through a concealed and computerized random number program [28]. A person who has no direct involvement in this trial will do the randomization process. Also, we note that the participants and attending physician (RA) can’t be blinded to the use of PHRs because the artefact is obvious, but the chief researcher (MT) and data analyst ([name]) are blinded to the participants during the trial. To minimize contamination of the trial, the subjects in the intervention arm will be required not to interact and share their DPHRs information with other participants in the control arm.

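### As written, no stated analysis of self-care conditions on the baseline score or the allocation factors, and the only stated covariate adjustment is a logistic regression that does not fit a continuous score

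*Protocol article*

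**What the plan says.** All references are to the Methods of the protocol article.

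- **Study Design** fixes the measurement times: "Repeated assessments will be conducted at two time points, including baseline and postintervention".
- **Trial Population and Recruitment Procedure** lists the self-care score, age, gender and employment status among the baseline data.
- **Randomization and Blinding** balances allocation on gender, employment and "age groups (=<30; 30-50; and =>50 years of age".
- **Analysis Plan** has four elements that bear on self-care:
  1. A linear mixed model is named for the effect of the tool on self-care. Its terms are not given.
  2. The next sentence says that the longitudinal data collection "will result in a repeat in the measure of analysis of variance using data from all trial assessment points".
  3. For group comparisons in general, a t "test will be used to compare the control and intervention groups", with chi-square for categorical variables.
  4. Adjustment for baseline characteristics and confounders is assigned to sequential logistic regression.

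**The concern.** With one pre-treatment and one post-treatment score, a repeated-measures ANOVA treats the baseline score as an outcome. Its group-by-time test is then the t test on change from baseline. That test uses the baseline, but less efficiently than a model with baseline as a covariate.

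The one place where the plan promises covariate adjustment uses a method for a categorical outcome. It cannot adjust a self-care score that is analysed as continuous, which the mixed model and the ANOVA both imply. So the adjustment that the plan intends does not reach the self-care score through any method that it states.

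At stake is precision in a trial of 72 people, and clarity about which result answers the study hypothesis. The change contrast, a post-score comparison and a baseline-adjusted comparison can give different p-values on the same data.

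A smaller, separate matter is that the age bands overlap. Patients aged exactly 30 or 50 belong to two bands, so their stratum is not defined by the text.

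**Working it through.** **Inputs from the document**

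- Test level: "All analyses will be 2-tailed and statistical significance is considered as a *P* value of ≤.05".
- Base sample size: "A sample size of 60, corresponding to the formula, has been estimated". At 1:1 allocation this is 30 per arm.
- Design values: "Considering confidence interval 95%, a power of 80%, and a dropout rate of 20%, 72 subjects will be required". The step from 60 to 72 is 60 × 1.20 and plays no part below.
- Effect size and SD: not given. The plan says only that the "sample size for this study was estimated based on the similar study in the country of Iran". The figure of 60 therefore cannot be reproduced; it can only be inverted.

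**Assumptions**

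- *Standardised difference d.* With 30 per arm, 58 degrees of freedom and two-sided 5%, the noncentral t gives 80% power at d = 0.736. The normal approximation is close: (1.960 + 0.842) × √(2/30) = 0.723.
- *Correlation ρ between baseline and 4-month score.* This is not given. The Outcome Measure section reports a correlation of 0.4 for the instrument but not its type, so a range is shown.

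**Variance per patient, relative to the post-score variance (equal variances at both times)**

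- Post-score comparison: 1
- Change score, or group-by-time test: 2(1 − ρ)
- Baseline as covariate: 1 − ρ²

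The last is below 1 for any ρ between 0 and 1. Its ratio to the change-score variance is (1 − ρ²) / [2(1 − ρ)] = (1 + ρ)/2, also below 1. The direction therefore does not depend on the assumed ρ.

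**Power with 30 per arm, d = 0.736, replacing d by d/√variance**

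| ρ | Variance, change | Variance, covariate | Ratio | Power, post-score | Power, change | Power, covariate |
|---|---|---|---|---|---|---|
| 0.3 | 1.40 | 0.91 | 0.65 | 80% | 65.8% | 83.6% |
| 0.4 | 1.20 | 0.84 | 0.70 | 80% | 72.5% | 86.4% |
| 0.5 | 1.00 | 0.75 | 0.75 | 80% | 80.0% | 89.9% |
| 0.7 | 0.60 | 0.51 | 0.85 | 80% | 95.1% | 97.5% |

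Above ρ = 0.5 the change contrast beats the post-score comparison. The covariate analysis beats both throughout.

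A simulation (4,000 runs, d = 0.723) confirms the order. At ρ = 0.4, power was 78% post-score, 72% change and 85% covariate. At ρ = 0.6 it was 78%, 86% and 93%.

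**Does naming a mixed model settle it?** Not by itself. With complete data at two times, a mixed model with free group, time and group-by-time terms has the change contrast as its interaction. Its group contrast at 4 months is the post-score difference. The plan handles missing values by multiple imputation, so each imputed data set is complete and this equivalence applies. The model reaches about the precision of the covariate analysis only if baseline means are constrained equal or baseline enters as a covariate. The text states neither, and its next sentence describes a repeated-measures ANOVA.

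**The case against.** The strongest objection is that the analysis named for self-care is a linear mixed model whose terms a condensed article may leave to a fuller plan. One version of it, with baseline means constrained equal, is as good as what is recommended here. This stands in part: unlisted terms alone would be no finding. But the article goes on to describe the analysis as a repeated-measures ANOVA and assigns adjustment to a model type that does not suit the score. Those are statements, not omissions.

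The logistic regression might be meant for adherence to planned visits, the other primary measure in the Abstract. If so, it may be suitable there, but self-care is left with no stated adjustment.

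A reader might infer several stronger things that the document does not support:

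- *That self-care will be tested by the t test.* The t test is listed for continuous variables in general.
- *That baseline is ignored.* The ANOVA uses it, inefficiently.
- *That power falls to about 39%.* This is the figure at ρ = 0.4 for the ANOVA's group main effect, which averages in the pre-treatment score. Nothing says that this effect would be read as the treatment test.
- *That the test runs at a known level below 5% because balanced factors are left out.* If those factors explained 5% to 20% of the variance, a nominal 5% test would run at about 4.4% to 2.8%. The document gives no figure for their prognostic strength, and a conservative test still controls the type I error.
- *That the overlapping bands cost precision.* They are an allocation ambiguity affecting only patients aged exactly 30 or 50.

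**Conclusion.** The point holds in a limited form. As written, no stated analysis of self-care conditions on the collected baseline score or on the three allocation factors. The stated adjustment method does not fit the outcome, and several non-equivalent analyses stand without one being named decisive.

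That baseline adjustment is more precise is certain for any correlation between 0 and 1. The size of the gain is illustrative. At assumed correlations of 0.3 to 0.7 it runs from about 18 percentage points of power (65.8% to 83.6%) down to about 2 (95.1% to 97.5%), relative to the change contrast. These figures rest on a back-solved effect size, an assumed correlation and 30 evaluable patients per arm. The further gain from gender, employment and age cannot be computed from the document. If the mixed model is already meant to be fitted with equal baseline means, the loss from baseline handling largely disappears and the text only needs to say so.

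The age-band overlap is real but minor.

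**What to change.** 1. State one primary analysis of the 4-month self-care score: either ANCOVA, or the planned mixed model with the baseline means of the two arms constrained equal. Use arm, baseline score, gender, employment and age band as terms. Report the adjusted mean difference with its 95% confidence interval.
2. For this outcome, use that model in place of the sequential logistic regression.
3. Label the t test and the unconstrained repeated-measures ANOVA as supportive.
4. State which band the allocation program uses for ages exactly 30 and 50, and use the same bands in the model. Recruitment is under way, so record the rule already in use rather than redraw the bands.

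The cost is a few sentences in the Analysis Plan and one clarification under Randomization and Blinding. All covariates are already collected, and the sample size does not change. The change should be made before outcome data are seen by arm.

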### Trial Population and Recruitment Procedure

The inclusion criteria for participants are as follows: the patient must be a male or female with type 2 diabetes, age between 20 and 70 years, with a minimum diabetes history of one year (according to the primary diagnosis date), must live in the city of Mashhad, must be fairly computer literate, and have access to the Internet. The included participants must be able to provide informed consent.

We excluded the already included participants, if they, for any reason, decided to terminate the participation, or were unable to actively continue the required cooperation, due to sickness, pregnancy, and etc.

The trial will be conducted in Mashhad City (Iran), with participants being recruited from one endocrinology practice unit. The number of diabetic patients is estimated to be above 120,000 in Mashhad [29]. We will start the study with the acquisition of baseline information including age, education level, gender, self-care score, HbA1c, weight, employment status, length of disease, and diagnosis date along with the information required to check the inclusion eligibility. Only the qualified participants will be given the consent form.

After signing the consent form, participants will be randomized into either the intervention or the control arm. After providing confirmed consent, a package including a copy of the consent form, welcome letter, and a take-home manual, along with step-by-step directions for using the website will be rendered manually to the participants. The participants are allowed to communicate with the trial team through email or telephone, sharing their questions and concerns. For assuring the quality of trial, the trial assistant will be trained during several sessions regarding the interaction with the website, the potential questions and answers of the participants, and the intervention process.

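### App-use dropout and elimination rules conflict with the intention-to-treat label, and multiple imputation alone may overstate the effect of assigning the app if stoppers' 4-month scores are not collected

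*Protocol article*

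**What the plan says.** Four statements in the Analysis Plan of the protocol article bear on this:

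- Missing data: "Missing values will be handled using multiple imputation [35". No predictors are named, and nothing is said about patients who stop using the app.
- Analysis principle: "All analyses will be done according to intention-to-treat principle".
- Dropout: "Dropouts from the study will be measured by no-use of the app tool for more than one month".
- Elimination: intervention patients have to record home glucose values "at least four times a week, otherwise, they are eliminated from the trial".

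Trial Population and Recruitment Procedure adds a further removal after inclusion: "We excluded the already included participants, if they, for any reason, decided to terminate the participation". It extends this to patients who can no longer cooperate actively.

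Two other sections say how and when the score is obtained. Data Collection: "Each participant will be requested to complete the questionnaire in-person at the reference clinic at the time of the scheduled diabetes follow-up". Study Design: "Repeated assessments will be conducted at two time points, including baseline and postintervention, over a 4-month trial period". Sample Size makes an allowance for loss: "Considering confidence interval 95%, a power of 80%, and a dropout rate of 20%, 72 subjects will be required".

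**The concern.** Intention-to-treat asks what assigning the app achieves, including in patients who abandon it. Both app-use rules can remove only intervention patients, because controls have no app. Applied as written, they leave an intervention arm made up of patients who kept using it.

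Standard multiple imputation assumes that a missing score resembles the observed scores of similar patients in the same arm. If stoppers' final scores are missing, the observed intervention scores all come from continuing users. Adding app use as a predictor would not help, because no retained patient has a comparable spell of non-use. With only two assessments, there is no intermediate score to inform the imputation either. The result would be close to the effect in continuing users, reported as intention-to-treat on the self-care outcome that carries the study hypothesis.

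**Working it through.** **The plan's own figure.** Sample Size starts from 60 and allows for 20% dropout. 60 × (1 + 0.20) = 72 reproduces the stated total; 60 / (1 − 0.20) = 75 does not. The allowance covers the whole trial. It does not forecast app stopping in the intervention arm. The loss that 72 actually covers is (72 − 60) / 72 = 16.7%.

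**Inputs.**
- 36 patients per arm (Sample Size).
- m, the share of the intervention arm with a missing 4-month score. Not in the article; 20% is assumed below (0.20 × 36 = 7.2 patients) and then varied.
- f, the share of the effect that stoppers keep: their mean gain over controls with the same baseline, divided by the continuing users' mean gain. Not in the article; varied.
- Imputation under missing at random, with baseline and arm in the model. This is an assumption, since the model is not stated.

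**Formula.** Set the continuing users' effect to 1. The true effect of assignment is (1 − m) + m·f. Within-arm imputation gives the missing patients the users' mean, so it estimates 1. The ratio of estimate to truth is 1 / (1 − m + m·f).

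**Results at m = 20%.**

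| f | 1 − m + m·f | Overstatement |
|---|---|---|
| 1 | 1.00 | 0% |
| 0.75 | 0.95 | 5% |
| 0.5 | 0.90 | 11% |
| 0.25 | 0.85 | 18% |
| 0 | 0.80 | 25% |
| −0.25 (worse than controls) | 0.75 | 33% |

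With f = 0 and other shares missing: 11% at m = 10%, 20% at m = 16.7%, 43% at m = 30%.

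**Simulation check.** 36 per arm, baseline-to-outcome correlation 0.5, 10 imputations, 1,500 trials per setting. The users' effect was 0.72 SD, which is what 30 per arm detects with 80% power: (1.960 + 0.842) × √(2/30) = 0.723. At m = 20%:
- f = 0: imputation gives 0.727 against 0.586 for the true effect of assignment, +24%.
- f = 0.5: 0.718 against 0.644, +12%.
- f = 1: 0.726 against 0.729, no bias.

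**Variations (m = 20%, f = 0).**
- Imputation model without arm: the imputed mean is the pooled observed mean, 28.8 / (28.8 + 36) = 0.444. The estimate is 0.8 + 0.2 × 0.444 = 0.889, and 0.889 / 0.8 = 1.11, so +11%.
- Eliminated patients left out altogether: the estimate is again the users' effect, about +25%. Standard imputation therefore corrects nothing here.
- Stoppers' clinic scores collected and analysed: nothing is imputed for them, and this bias is 0%.

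**The case against.** The strongest reply is that stopping the app does not make the score missing. The questionnaire is completed on paper at the clinic, every participant is asked for it, and reminders and free visits or tests are planned. If stoppers attend and are analysed, the problem disappears. That stands. However, the Analysis Plan classes these same patients as dropouts or eliminates them, and the article does not say that they are still assessed. Limitations itself expects that dropout could cost substantial data.

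Second, the imputation model is not described, and a condensed article may leave it to an analysis plan that is not shown. That also stands: missing detail is no fault here, and the figures above are conditional on a model. The clash between the app-use rules and the intention-to-treat statement is different, because both are written in the same section.

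Third, the rules rather than the imputation produce the bias. This is largely right. The rules create the missing scores, and imputation merely fails to repair the loss. The first remedy therefore has to address the rules.

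Fourth, scores may be missing for other reasons, such as sickness or pregnancy, and a patient who is inactive for just over a month of a 4-month trial may have used the app for most of it. Both are fair. Not every missing score belongs to a stopper, and a retained effect of zero is an extreme assumption.

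**Conclusion.** The point holds conditionally. The app-use dropout and elimination rules, and the exclusion after inclusion, do not fit the stated intention-to-treat principle. If stoppers' 4-month scores are lost as a result, standard imputation that includes arm probably overstates the effect of being assigned the app. With 20% of the intervention arm missing, the size is 0% to 25% for a retained effect between all and none, and about 11% at half. It exceeds 25% only if stoppers end worse than controls with the same baseline.

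A reader might infer that the plan's effect will be overstated by a quarter. The article does not support that. The figure needs 20% loss in the intervention arm specifically, every stopper's score missing, imputation within arm, and no retained benefit. None of these is stated. Nor does the article show that the type I error is inflated: that needs an assumed deficit in patients who stop, and the article gives no figure for one.

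**What to change.** First, reconcile the app-use dropout and elimination rules in the Analysis Plan, and the exclusion in Trial Population and Recruitment Procedure, with intention-to-treat. State that every available 4-month self-care score is analysed in the assigned arm whatever the app use, and that patients who stop are still asked for the clinic questionnaire. App use can still be reported descriptively.

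Second, for intervention patients who stopped and whose score is still missing, add a sensitivity analysis that imputes from the control-arm distribution given baseline (jump to reference). Report it beside the standard multiple imputation. It should not become a second condition for claiming an effect.

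The cost is some wording, follow-up of stoppers at a visit that the plan already asks of everyone, and one more imputation run. The control-based estimate is conservative. At 20% missing it returns 0.8 of the users' effect whatever stoppers keep. That is correct if they keep none, 11% too low if they keep half (0.8 / 0.9 = 0.89), and 20% too low if they keep all (0.8 / 1.0). Showing both analyses lets the reader see how far the conclusion depends on what stoppers are assumed to retain.
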